## Abstract

**Introduction:**

Patients with atrial fibrillation experience an irregular heart rate and have an increased risk of stroke; prophylactic treatment with anticoagulation medication reduces this risk. Direct-acting oral anticoagulants (DOACs) have been approved providing an alternative to vitamin K antagonists such as warfarin. There is interest from regulatory bodies on the effectiveness of medications in routine clinical practice; however, uncertainty remains regarding the suitability of non-interventional data for answering questions on drug effectiveness and on the most suitable methods to be used. In this study, we will use data from Apixaban for Reduction in Stroke and Other Thromboembolic Events in Atrial Fibrillation (ARISTOTLE)—the pivotal trial for the DOAC apixaban—to validate non-interventional methods for assessing treatment effectiveness of anticoagulants. These methods could then be applied to analyse treatment effectiveness in people excluded from or under-represented in ARISTOTLE.

**Methods and analysis:**

Patient characteristics from ARISTOTLE will be used to select a cohort of patients with similar baseline characteristics from two UK electronic health record (EHR) databases, Clinical Practice Research Datalink Gold and Aurum (between 1 January 2013 and 31 July 2019). Methods such as propensity score matching and coarsened exact matching will be explored in matching between EHR treatment groups to determine the optimal method of obtaining a balanced cohort.

Absolute and relative risk of outcomes in the EHR trial-analogous cohort will be calculated and compared with the ARISTOTLE results; if results are deemed compatible the methods used for matching EHR treatment groups can then be used to examine drug effectiveness over a longer duration of exposure and in special patient groups of interest not studied in the trial.

**Ethics and dissemination:**

The study has been approved by the Independent Scientific Advisory Committee of the UK Medicines and Healthcare Products Regulatory Agency. Results will be disseminated in scientific publications and at relevant conferences.

Strengths and limitations of this studySelection of electronic health record patients matched to the randomised controlled trial (RCT) patients allows assessment of the ability of non-interventional methods to detect effectiveness of treatments for stroke prevention in atrial fibrillation (AF) within an RCT-analogous population.Combined Clinical Practice Research Datalink (CPRD) Gold and Aurum population broadly representative of the patients prescribed apixaban and warfarin for AF in routine clinical practice in the UK.Some of the criteria that were assessed for ARISTOTLE eligibility may not be well recorded in CPRD.Adherence to medication will need to be assessed based on proxy variables (time covered by prescription for the direct-acting oral anticoagulants, time in therapeutic range based on international normalised ratio measurements for warfarin); the different nature of these proxy variables means the adherence estimates may not be comparable.Ascertainment of outcomes via CPRD is based on recording as part of routine clinical care rather than for specifically detecting study outcomes.

## Introduction

### Background and rationale

Atrial fibrillation (AF) is a common cause of cardiac arrhythmia with symptoms including palpitations, fainting and shortness of breath; however, some patients may be asymptomatic. The prevalence of AF in the UK is estimated to be around 3%,^1^ increasing from 0.2% in people aged 45–54 years to 8.0% in those 75 and older.^2^ The lack of organised atrial contraction in AF can lead to the formation of thrombi, meaning that patients with AF have a fivefold higher risk of stroke which is an important cause of morbidity and mortality.^3–5^

Current UK guidelines recommend use of prophylactic treatment with anticoagulation medication to reduce the risk of stroke. Warfarin, a vitamin K antagonist (VKA) and the previous standard anticoagulant treatment, has many treatment and dietary interactions requiring frequent monitoring of a patient’s international normalised ratio (INR), to maintain anticoagulant activity within a narrow range (2.0–3.0). Low levels put the patient at a higher risk of stroke while high levels lead to a higher risk of bleeding.^6^ In 2011, the first direct-acting oral anticoagulant (DOAC) dabigatran was approved for the treatment of AF in the European Union (EU); it was anticipated to provide easier to manage long-term anticoagulation therapy for patients with AF given the complex safety profile of warfarin. ARISTOTLE, a pivotal randomised controlled trial (RCT) of the DOAC apixaban, demonstrated superiority over warfarin for both prevention of stroke and safety (major bleeding) among individuals with AF.^7^

The generalisability of the ARISTOTLE trial is limited by the strict eligibility criteria; evidence on apixaban’s treatment effect is therefore lacking for patients who would not have met the eligibility criteria such as those at increased bleeding risk or with severe comorbid conditions. The regulatory environment now demands evidence of treatment effectiveness outside the confines of randomised trials.^8 9^ Non-interventional data sources have the potential to overcome many of the RCT limitations given that they contain data for a wide spectrum of patients treated with the drug in routine care, including patients who would have been not eligible for trials. Data collected as part of routine patient care such as electronic health record (EHR) provide a valuable opportunity to obtain evidence on the effectiveness of apixaban in a routine care setting. A key problem with using these data is that the absence of randomisation leaves them highly susceptible to confounding making it difficult to have confidence in the results.

To address this lack of confidence, this study will apply innovative matching approaches to create a trial-analogous non-interventional cohort for analysis. Records from UK EHRs will be matched to ARISTOTLE patients before using methods for matching between treatment groups within the non-interventional EHR data, creating an EHR population similar to the trial population that is well balanced by treatment group. If successful, estimates of effectiveness and safety of apixaban obtained from analysis of this ARISTOTLE-analogous cohort should be comparable with the results from the ARISTOTLE trial. The non-interventional analysis methods used to obtain these results may then be used to reliably estimate effects in understudied AF patient groups.

## Aims and objectives

The aims of this study are (1) to measure the association between anticoagulation treatments for stroke prevention in AF and time to stroke, systemic embolism (SE), myocardial infarction (MI), major bleeding and mortality among an ARISTOTLE-analogous cohort of patients from UK EHRs, and (2) to develop a methodological framework with in-built validation for using observational EHRs to answer questions about DOAC risks and benefits in patients not included or under-represented in the RCTs.

The specific objectives are to:

Objective 1. Check comparability of EHR data and robustness of methods for measuring stroke prevention medication effectiveness in an ARISTOTLE-analogous cohort using data from EHR data and by comparing with ARISTOTLE results.

Objective 2. Extension of trial findings: measure treatment effects of apixaban in patient groups excluded from ARISTOTLE.

Objective 3. Comparative effectiveness: compare treatment effectiveness between multiple individual anticoagulants (warfarin, apixaban, rivaroxaban, dabigatran) in ARISTOTLE-eligible cohorts and in patient groups excluded from ARISTOTLE.

## Methods and analysis

Figure 1 (figure adapted from a study in real-world effects of medications for chronic obstructive pulmonary disease^10^) provides an overview of the study, covering the objectives and data sources used, and how RCT data will be used in Objective 1 to validate methods for analysing effectiveness of treatments for stroke prevention in AF in non-interventional data. Should Objective 1 prove successful the validated methods will be applied to unanswered questions in Objectives 2 and 3.

**Figure 1 F1:**
[figure not shown]
Overview of study objectives and sources of data for the real-world effects of medications for stroke prevention in AF study. AF, atrial fibrillation; CPRD, Clinical Practice Research Datalink; EHR, electronic health record; RCT, randomised controlled trial. (A) Work performed by others prior to this study. ARISTOTLE: RCT that investigated effectiveness and safety of apixaban vs warfarin in prevention of stroke and systemic embolism in AF patients. RCTs results inform clinical practice despite only a subset (based on trial inclusion and exclusion criteria) of the total population of AF patients being included in the RCTs of stroke prophylaxis treatments. (B) Work to be performed as part of this study. (1) Objective 1. A cohort of ARISTOTLE-analogous patients will be selected from UK EHRs (CPRD Gold and Aurum), by matching EHR patients prescribed apixaban to the apixaban patients included in the trial on baseline characteristics. EHR patients prescribed warfarin will then be matched to the trial-analogous EHR apixaban patients. An analysis of the effectiveness of apixaban vs. warfarin on prevention of stroke/systemic embolism will then be performed on this ARISTOTLE-analogous EHR cohort. If the results obtained are comparableto those obtained in ARISTOTLE, this will serve as a validation step, showing that data from the non-interventional CPRD Gold and Aurum sources can reliably be used to study stroke prevention treatment effects in AF. (2) Objective 2. The validated analysis techniques used for Objective 1 will then be used to study UK EHR patients who would not have been eligible for inclusion in an RCT or are under-represented in RCTs due to their age or presence of other comorbidities, for whom the comparative effects of anticoagulants in stroke prevention in AF is unclear.(3) Objective 3. The validated analysis techniques used for Objective 1 will then be used to compare effectiveness of apixaban vs warfarin, apixaban vsrivaroxaban and apixaban vs dabigatran.

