#### ARISTOTLE

ARISTOTLE was a randomised, double-blind trial completed in 2011, comparing apixaban with warfarin in the prevention of stroke and SE. The trial included 18 201 patients with AF and at least one additional risk factor for stroke. The trial was designed to test for non-inferiority of apixaban compared with warfarin, and showed apixaban superiority for (1) the primary outcome of stroke or SE (HR 0.79, 95% CI 0.66 to 0.95),^7^ (2) the safety endpoint of major bleeding (HR 0.69, 95% CI 0.60 to 0.80), and (3) death from any cause (HR 0.89, 95% CI 0.80 to 0.99). The ARISTOTLE findings led to the National Institute for Health and Care Excellence (NICE) guidelines on stroke prophylaxis in patients with AF recommending apixaban as a treatment. Baseline patient characteristics from ARISTOTLE will be used in selection of participants in Objective 1.

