The absolute rates and HR for the outcomes of interest (time to: stroke/SE, MI, major bleeding and mortality) will then be calculated. For the primary outcome (time to stroke/SE) the EHR results will be validated against the ARISTOTLE trial results using the criteria detailed in the Statistical Analysis section (Validation of observational results against ARISTOTLE data).

#### Objective 2

We will select patient groups who would not have been included in ARISTOTLE (and therefore would not have been included in the Objective 1 cohort) or who are under-represented in ARISTOTLE. Specifically, this will include patient groups such as patients with an AF diagnosis in the EHR cohort meeting these additional criteria:

Severe comorbid condition: disease with a likelihood of causing death within 1 year or reasons making participation unpractical (such as dementia).

When matching the apixaban and warfarin patients within the patient groups for this objective, additional baseline variables will be considered compared with the list specified for Objective 1, Step 2; namely the H, A, and B components of the HAS-BLED score (Hypertension, Abnormal renal/liver function, Stroke, Bleeding history or predisposition, Labile INR, Elderly (>65 years), Drugs/alcohol concomitantly) not included for Objective 1 matching due to being ARISTOTLE exclusion criteria. In these special patient populations the same outcomes as Objective 1 will be assessed, with absolute and relative rates calculated separately in each special patient group.

#### Objective 3

We will select all patients with AF who have a prescription for apixaban, warfarin, rivaroxaban or dabigatran in the treatment period (between 1 January 2013 and 31 July 2019). The ARISTOTLE trial criteria will be applied, followed by matching the warfarin, rivaroxaban and dabigatran ARISTOTLE-eligible EHR patients in turn to the trial-eligible EHR apixaban patients following the methodology outlined in Objective 1, Step 3. This process will result in the creation of three trial-eligible EHR cohorts: warfarin users matched to apixaban users, rivaroxaban users matched to apixaban users and dabigatran users matched to apixaban users. Matched cohorts of excluded patient groups will also be constructed to enable pairwise comparisons of treatment effects in these groups using the method outlined in Objective 2. In all cohorts, the same outcomes as Objective 1 will be assessed with both absolute and relative treatment effects compared.

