#### Validation of observational results against ARISTOTLE data

In Objective 1 alone, we will validate the findings from our primary analysis against ARISTOTLE by determining whether results are compatible with the trial results. ARISTOTLE demonstrated superiority of apixaban over warfarin for the primary endpoint (HR 0.79, 95% CI 0.66 to 0.95).^7^ The treatment effect seen with EHR data may be weaker than that seen in ARISTOTLE.

An analysis of EU patients in ARISTOTLE showed a smaller treatment difference for the primary endpoint and death: HR for stroke/SE 0.92 (95% CI 0.56 to 1.52), all-cause death 0.89 (95% CI 0.68 to 1.18). The European Medicines Agency Assessment Report suggested the smaller treatment effect may have been due to superior INR control in the warfarin arm of the EU subgroup (median time in therapeutic range (TTR) 68.93%)^15^; this study could provide additional evidence on this point.

Either a result of superiority or non-inferiority will be considered compatible with ARISTOTLE results. We have set two criteria that must be met to conclude results are consistent with the trial result:

The effect size must be clinically comparable with the ARISTOTLE findings; the HR for time to stroke/SE with the EHR must be between 0.69 and 0.99. This range is not symmetrical around the ARISTOTLE estimate of 0.79 as it is anticipated the treatment effect in routine clinical care may be weaker than that seen in the optimised setting of a clinical trial.The upper limit of the 95% CI for the rate ratio must be less than 1.52 (upper limit in the EU subgroup of ARISTOTLE).

In addition, if the upper limit of the 95% CI is less than 1 then superiority of apixaban versus warfarin will be concluded.

In order to understand the extent to which the EHR population resembles the ARISTOTLE trial population the absolute event rates of the outcomes will be compared.

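### A pass in Objective 1 tests the matching for apixaban vs warfarin only, yet the plan carries the label of validated techniques to apixaban vs rivaroxaban and apixaban vs dabigatran, which have no benchmark

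*Protocol article*

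**What the plan says.** The benchmark is described in the protocol article under Setting/data sources, ARISTOTLE, as a trial "comparing apixaban with warfarin in the prevention of stroke and SE", with a result for stroke or systemic embolism of "HR 0.79, 95% CI 0.66 to 0.95".

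Under Validation of observational results against ARISTOTLE data, the scope is explicit: "In Objective 1 alone, we will validate the findings from our primary analysis against ARISTOTLE". Two criteria follow: "the HR for time to stroke/SE with the EHR must be between 0.69 and 0.99", and "The upper limit of the 95% CI for the rate ratio must be less than 1.52". Both refer to apixaban against warfarin.

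The opening of Methods and analysis then makes the later objectives depend on that result: "Should Objective 1 prove successful the validated methods will be applied to unanswered questions in Objectives 2 and 3". The Figure 1 legend goes further in two ways. It takes comparability with ARISTOTLE as showing that the two primary care databases are reliable for studying stroke prevention treatment effects in atrial fibrillation generally. It also says that the "validated analysis techniques used for Objective 1 will then be used to compare effectiveness of apixaban vs warfarin, apixaban vsrivaroxaban and apixaban vs dabigatran".

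Under Selection of participants, Objective 3, users of warfarin, rivaroxaban and dabigatran are each matched in turn to apixaban users "following the methodology outlined in Objective 1, Step 3".

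Under Plan for addressing confounding, the argument that channelling bias should be avoided is made for Objective 1. A general sentence then accepts that unmeasured confounding may remain and says it will be explored.

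**The concern.** Whether matching is adequate depends on the prescribing decision being modelled. Apixaban or warfarin is one decision; which DOAC to prescribe is another, and the unmeasured reasons behind it may differ. A method that recovers the trial result for the first has not been tested on the second.

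The abstract and the end of the Introduction speak of extending the methods to longer exposure and to understudied patient groups. Objective 3 asks for more: it changes the comparator drug. The article describes no rivaroxaban or dabigatran benchmark, no negative control and no other check specific to a DOAC-DOAC contrast.

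What is at stake is the evidential status of Objective 3. Under Dissemination plans, relevant results are to go to the guideline body and the medicines regulator. If a modest difference between two DOACs arrives with the statement that it was obtained by validated techniques, readers may give it more weight than the design supports.

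**Working it through.** **Does the test see the DOAC-DOAC contrast?** The plan states no figure for this contrast to reproduce, so the argument is structural first. Let b(A), b(W) and b(R) be the log-scale unmeasured prognosis of matched apixaban, warfarin and rivaroxaban users.

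- Residual bias in Objective 1: b(A) − b(W).
- Residual bias in apixaban vs rivaroxaban: b(A) − b(R).
- Both criteria are functions of the apixaban-warfarin estimate and its confidence interval. Neither contains b(R), nor the corresponding term for dabigatran.

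So no value of b(R) can change the pass or fail result. This needs no numerical assumption.

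**Illustration 1 (all inputs assumed).** Take a binary unmeasured factor with outcome risk ratio RR. The bias factor is (1 + p1(RR − 1)) / (1 + p0(RR − 1)), where p1 and p0 are its prevalences in the two groups. Let prevalence be 10% in apixaban users, 10% in warfarin users and 20% in rivaroxaban users.

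- Apixaban vs warfarin: the factor is 1, so a true 0.79 reads 0.79. From the ARISTOTLE interval, SE = (ln 0.95 − ln 0.66)/(2 × 1.96) = 0.093. With an SE of that size the upper limit is 0.79 × exp(1.96 × 0.093) = 0.95. Both criteria are met.
- Apixaban vs rivaroxaban with a true HR of 1.00 and RR = 2: 1.1/1.2 = 0.917.
- Over RR 1.5 to 3 the spurious HR runs from 0.955 to 0.857. With prevalences of 20% vs 40% it runs from 0.917 to 0.778.

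**Illustration 2 (all inputs assumed).** RR = 2, prevalence 30% vs 20%: bias 1.3/1.2 = 1.083. If the same bias sat in apixaban vs warfarin, 0.79 × 1.083 = 0.856, still inside 0.69 to 0.99. For a true DOAC-DOAC HR of 1.00, the chance of a two-sided 5% result, with SE = 2/√events, is:

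| Events (assumed) | SE | Shift = ln 1.083 / SE | Chance of a significant result |
|---|---|---|---|
| 600 | 0.0816 | 0.98 | about 17% |
| 1200 | 0.0577 | 1.39 | about 28% |

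**Would adding rivaroxaban-warfarin and dabigatran-warfarin cohorts settle it?** Suppose each warfarin contrast were judged by a window of the same relative width. Around 0.79 that width is 0.69/0.79 = 0.87 to 0.99/0.79 = 1.25. The DOAC-DOAC bias is the ratio of the two tolerated biases, so both could pass with a bias anywhere from 0.69/0.99 = 0.70 to 0.99/0.69 = 1.43. The matched warfarin patients would also differ between the two contrasts, so b(W) need not cancel.

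**The case against.** Several points on the other side are fair.

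- **The label is attached to techniques, not results.** The protocol calls its methods and analysis techniques validated and confines validation to Objective 1. A reader might infer that it declares the DOAC-DOAC comparisons themselves validated. The text does not say that. What stands is that the label is carried to contrasts the test never involved.
- **The matching list is mostly general.** A reader might infer that the covariates were built for the warfarin contrast and must be re-used unchanged. Step 2 justifies them by their expected influence on the outcomes. Only prior VKA exposure and its duration, and labile INR, are specific to warfarin. Step 3 adds data source, socioeconomic status and comorbidities as covariates to consider, and the list is open. What remains untested is whether such a set suffices for the choice between DOACs.
- **Residual confounding is acknowledged.** The general caveat is not limited to Objective 1, and its detail may properly sit in a fuller document. But a caveat is not a check, and it does not withdraw the label.
- **The window is not a measure of tolerated bias.** Reading 0.87 to 1.25 as bias assumes a true UK HR of exactly 0.79. The plan widened the window because the effect may be weaker in routine care, and it cites 0.92 in the EU subgroup. Against 0.92 the range is 0.69/0.92 = 0.75 to 0.99/0.92 = 1.08. That concerns window width, a separate question.
- **The main focus is unaffected.** The limitations section names validation against ARISTOTLE as the main aim, and nothing here touches it.

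**Conclusion.** The point holds as one about what Objective 3 can claim. A pass in Objective 1 would support the quality of the data and the ascertainment of outcomes, and would support the matching for apixaban vs warfarin. It cannot show that matching is adequate for apixaban vs rivaroxaban or apixaban vs dabigatran. The third Objective 3 comparison, apixaban vs warfarin in trial-eligible patients, is close to the tested contrast and is not in question.

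The documents do not fix the size of any bias. The spurious HRs of 0.955 to 0.778 and the 17% and 28% error rates rest wholly on assumed prevalences, risk ratios and event counts. They show only that a misleading DOAC-DOAC difference can coexist with a pass. They do not show that prescriber selection of this size exists in these data, or that the DOAC-DOAC results will be wrong.

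No stated figure needs correcting. The change is worth making because the present wording misstates the standing of two of the three Objective 3 comparisons.

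**What to change.** 1. In the opening of Methods and analysis and in the Figure 1 legend, restrict the word validated, and the conclusion that the data are reliable, to apixaban vs warfarin. The Objective 3 selection text does not use the label, and the use in Objective 1, Step 4 is already correct.
2. Under Selection of participants, Objective 3, state that the DOAC-DOAC results have no randomised benchmark and will be reported as exploratory with respect to residual confounding.
3. Consider choosing the matching covariates for each DOAC pair separately.
4. Optionally, build rivaroxaban-warfarin and dabigatran-warfarin matched cohorts from patients already selected, as a one-sided falsification check. Disagreement with a suitable external trial would count against the DOAC-DOAC result. Agreement would give partial support only, because the warfarin sets differ and the tolerances compound.

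Items 1 and 2 cost only wording, and the price is weaker claims for Objective 3. Item 3 adds some modelling work. Item 4 costs more than two extra cohorts: it needs other trials' results and eligibility criteria, which are not in this document, and agreement limits set for those trials.
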